#### Statistical Analysis Plan

Descriptive statistics (means, SD, counts, and percentages) will be calculated for all variables of interest overall and stratified by age group. Difference in difference models will be used to evaluate changes in frequencies and rates for pre versus post intervention effects within the intervention groups and for passive control versus active control versus test effects. Linear regression will be used to evaluate continuous outcomes and logistic regression will be used to evaluate binary outcomes. The primary hypothesis for all participants is that the test intervention group will have a lower number of restorative dental care procedures received than the active control group during the 18 months post intervention start date. For children less than 36 months old, the primary hypothesis is that the test intervention will increase toothbrushing frequency more than the active control intervention and no change in passive control group will be observed 10 months post intervention start date. Secondary hypotheses are that member satisfaction and oral health-related quality of life of the participants will be greater and that dental care costs and dental caries will be lower in the test intervention and active control than in the passive control.

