#### The Toothbrushing Kit

The kit contains supplies for adults and for children, specifically 7x .85 oz. tubes of toothpaste (1500 parts per million sodium fluoride), 3 adult-size toothbrushes, 1 toothbrush each for a child ages 4-24 months, 2-4 years, and 5-7 years. This quantity was chosen because the average family served by Advantage Dental Services has 3 or 4 children. In addition to the supplies, the kit includes a single-page removable “cling sheet” with instructions to brush twice a day with an age-appropriate amount of fluoride toothpaste depicted by illustration, and information about how to request additional supplies if needed. Each family receives three kits over the 9-month intervention period.

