#### Data Collection

Data on type, amount, and cost of dental care will be collected through health information systems of the dental care organization (Enrollment and Claims Database) for all participants. For children less than 36 months old, information on the children’s toothbrushing behaviors, parent-rated oral health and oral health-related quality of life of the child, child’s juice consumption and frequency, parental self-efficacy, intention and attitudes regarding brushing the child’s teeth, parent educational level, and their opinions about each component of the intervention will be collected through telephone interviews with parents/caregivers at baseline and at the end of the intervention. For children less than 36 months old at baseline, information on the presence of untreated dental caries (cavitated caries in permanent or primary teeth) will be collected through a clinical examination 24 months after the study start date. Fidelity information will be obtained through examination of internal records of mailings, returned mail receipts, and telephone calls.

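### Pre-to-post changes within an arm are listed as intervention effects, and a no-change clause for passive control sits in the primary brushing hypothesis; neither can separate the program from ageing

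*Protocol article*

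**What the plan says.** The Statistical Analysis Plan section names one class of model and two targets. The first is stated thus: "Difference in difference models will be used to evaluate changes in frequencies and rates for pre versus post intervention effects within the intervention groups". The second, joined to it in the same sentence, is "and for passive control versus active control versus test effects". Both are called effects.

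The hypotheses that follow are mostly comparisons between randomized arms:
- For all participants: "the test intervention group will have a lower number of restorative dental care procedures received than the active control group".
- For children under 36 months: "the test intervention will increase toothbrushing frequency more than the active control intervention".
- The secondary hypotheses set test and active control against passive control.

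One statement is not a comparison between arms. The primary brushing hypothesis also requires that "no change in passive control group will be observed 10 months post intervention start date".

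Brushing is measured by "telephone interviews with parents/caregivers at baseline and at the end of the intervention" (Data Collection). The Results section dates these interviews to June-July 2014 and May 2015, about 10 to 11 months apart. The eligibility criteria set no lower age limit. The smallest brush in the kit is for children from 4 months ("1 toothbrush each for a child ages 4-24 months").

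**The concern.** The null hypothesis of a within-arm pre-to-post test is that nothing changed over calendar time in that arm. In very young children, 10 to 11 months is a large part of life. Some may have no brushing routine at the first interview and have one at the second, with or without the program. Any such drift is absorbed into the within-arm estimate, which the plan labels an intervention effect. Randomization protects the comparison between arms but not this one.

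The same drift bears on the passive-control clause. If brushing rises with age, that part of the primary hypothesis fails even when the program works as hoped. If the test is not significant, that does not show that nothing changed.

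At stake is how the results are read. The Discussion says the evaluation will inform whether the program is sustained and expanded. A rise in brushing within the test or active control arm, reported as an effect, could be taken as support when it is only development.

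**Working it through.** **1. The plan's own figures.** The Sample Size section gives a control proportion of .6, alpha .025 and beta .20, with 39 and 66 per group for effect sizes of 50% and 40%. Read the effect sizes as relative changes (.6 to .9 and .6 to .84), take alpha as two-sided, and use the pooled formula without continuity correction:

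n = [z(.9875)·√(2p̄(1−p̄)) + z(.80)·√(p1(1−p1) + p2(1−p2))]² / (p1−p2)², with z(.9875) = 2.241 and z(.80) = 0.842.

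This gives 38.3 and 65.2, which round up to 39 and 66. The caries figures (.5 to .35 and .5 to .30) give 205.2 and 112.8, that is 206 and 113. All four reproduce, so two-sided alpha .025 is used below.

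**2. Inputs for the within-arm test.** From the article: n = 150 interviewed per arm, proportion .6, alpha .025. Assumed, because the article gives neither: a natural drift d of 0 to 20 percentage points, equal in all arms, and a within-child correlation ρ of 0, .3 or .5. The program effect is set to zero.

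**3. Formula (McNemar-type paired test).** With p0 = .6 and p1 = .6 + d:
- p11 = p0·p1 + ρ·√(p0(1−p0)p1(1−p1))
- discordant proportion m = p0 + p1 − 2·p11
- the test rejects when the absolute observed change exceeds 2.241·√(m/n)
- the standard error of the change under drift is √((m − d²)/n)

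*Worked case, d = .10 and ρ = .3.* p11 = .487 and m = .325. The critical change is 2.241·√(.325/150) = .104, and the standard error is √((.325 − .010)/150) = .0458. Rejection = P(Z > (.104 − .100)/.0458) = P(Z > 0.10), about 46%.

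**4. Results with no program effect, ρ from 0 to .5** (simulation, with the normal approximation as a check; the 2-point row is from the approximation):

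| Assumed drift | Within-arm rejection |
|---|---|
| 0 points | 2.5% |
| 2 points | 3.4-4.4% |
| 5 points | 9-16% |
| 10 points | 33-63% |
| 15 points | 70-96% |
| 20 points | 94-100% |

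The difference in paired changes between two such arms rejects in 2.5-2.8% of trials for drifts from 0 to 20 points.

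**5. How such a drift could arise (illustration only).** Suppose ages are uniform over 0 to 36 months, children under 4 months are not brushed at baseline, and all others stay at .6. The unbrushed share is 4/36 = 11%. The baseline proportion is then .6 × 32/36 = .533, and the drift to .600 is 6.7 points. Simulated within-arm rejection is about 16-24% at alpha .025 for correlations of .2 to .5.

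**6. The passive-control clause.** The rates in step 4 apply to this arm too. With no true change, the smallest significant change is 2.241·√(m/150). At ρ = 0, .3 and .5, m is .48, .336 and .24, which gives 12.7, 10.6 and 9.0 points. A non-significant result is therefore compatible with a sizeable real change.

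**The case against.** The strongest reply is that the sentence describes difference in difference. In that method the change within each arm is only the first difference, and the contrast between arms is the estimand. No alpha, criterion or decision rule is attached to a within-arm test, and such detail may belong to an analysis plan that is not shown. Every hypothesis of program benefit compares arms, and so does the research question. Much of this stands. It does not remove the point, because the sentence sets the within-arm change beside the between-arm effects as a target of its own, and the passive-control clause puts a within-arm statement inside a primary hypothesis.

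A reader might infer more than the article supports, in four ways:
- *The main conclusions are inflated.* They are not. The between-arm contrasts keep their alpha under equal drift.
- *Ageing will certainly push rejection far above alpha.* This depends on a drift rate that the article does not give. At 2 points the excess is slight. The 11% in the illustration rests on a brush-size label and an assumed age distribution.
- *Restorative care would show a false benefit.* Ageing would more probably raise restorative care, so a within-arm rejection would point away from benefit. The stated hypothesis for that outcome is test versus active control.
- *The program's effect in older children will be claimed from within-arm change.* The passive control holds only families with children under 36 months, so for older children no randomized contrast with an untreated arm exists. The plan, however, states no within-arm hypothesis for them. The missing untreated arm is a separate design matter.

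**Conclusion.** The point holds as a defect of wording that should be corrected. Within-arm changes are named as intervention effects, and an absence of change in one arm is made part of a primary hypothesis, although neither can distinguish the program from ageing. The bias is negligible if brushing drifts by about 2 points, material at 5 points and serious at 10. These figures assume 150 analyzed per arm, a starting proportion of .6, equal drift in all arms and a within-child correlation between 0 and .5. The concern is confined to within-arm statements, chiefly about brushing.

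**What to change.** Make two changes of wording in the Statistical Analysis Plan section.

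1. Replace the within-arm target with a statement such as: *Intervention effects are estimated only from between-arm (arm-by-time) contrasts, namely test versus active control and, in children under 36 months, each of these versus passive control. Pre-to-post changes within an arm are reported descriptively and are not interpreted as intervention effects.*
2. In the primary brushing hypothesis, replace the no-change clause for passive control with the contrasts of test and of active control against passive control. Without this second change the plan would bar within-arm inference while keeping a within-arm claim in a primary hypothesis.

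The cost is a few sentences. No new data are needed, the contrasts are already among those the plan names, and the between-arm comparisons lose no power. Because a primary hypothesis is reworded, the change should be dated and made before the final interview data are analyzed by arm, and the plan should say how its alpha covers the contrasts with passive control.

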### Randomization and Blinding

Families will be randomized with equal probability to one of three study conditions using computer-generated random numbers. A biostatistician at the University of Washington using a dataset containing only family identification codes and without personal identifying information will generate the allocation schedule for random assignment. The treatment allocation for each participant will be kept in Seattle, and the biostatistician will reveal the treatment allocation to local investigators when they are ready to implement the program. Personnel involved in the delivery of the intervention and trial participants will not be blinded to group allocation. Interviewers will be blinded to group allocation.

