#### Mediators and Confounders

Mediators of the effect of the intervention on the primary outcomes will be the number of toothbrushing kits and instructions (mail and telephone) delivered. Parent’s age, family size, and race/ethnicity will be considered confounders and explored for effect modification. Among children less than 36 months old, potential mediators to be examined are: parent/caregiver’s self-efficacy, attitudes, intention, skills, and norms in relation to brushing their child’s teeth. Additionally, for this group, parental educational level and child’s juice consumption will be considered confounders.

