### Statistical Analysis

#### Sample Size

Sample size for dental care outcomes was not calculated, as the sample size of 20,000 participants was deemed sufficient to observe an effect of the intervention on the primary outcome of restorative care utilization.

Prevalence and effect size estimates for frequency of twice daily toothbrushing among children less than 36 months old at baseline was based on that reported in a study in a similar population [25]. Assuming a proportion in the passive control group of .6, alpha = .025, beta = .20, the required sample sizes for effect sizes of 50% and 40% are 39 and 66 participants in each group. We decided on a sample size of 150 participants in each group.

Untreated dental caries estimate was based on that reported in a study in a similar population [1]. Assuming a proportion of children with dental caries experience in the passive control group of .5, alpha = .025, beta = .20, the required sample sizes for effect sizes of 30% and 40% are 206 and 113. We decided on a sample size of 210 participants in each group.

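### Toothbrushing outcome: difference-in-differences in randomized arms is less precise than a follow-up comparison adjusted for baseline brushing and child age, and is not the analysis the sample size reproduces

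*Protocol article*

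**What the plan says.** All references are to the protocol article.

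- **Model.** Statistical Analysis Plan: "Difference in difference models will be used to evaluate changes in frequencies and rates for pre versus post intervention effects within the intervention groups". The same sentence goes on to the comparison of the three conditions with one another. The next sentence adds: "Linear regression will be used to evaluate continuous outcomes and logistic regression will be used to evaluate binary outcomes". Neither names the baseline value or the child's age as a model term.
- **Allocation.** Randomization and Blinding: "Families will be randomized with equal probability to one of three study conditions using computer-generated random numbers".
- **Hypotheses.** Restorative care is worded as a post-start count: "lower number of restorative dental care procedures received than the active control group during the 18 months post intervention start date". For children under 36 months, brushing is worded as a change, assessed 10 months after the start: "the test intervention will increase toothbrushing frequency more than the active control intervention and no change in passive control group will be observed".
- **Baseline data.** Data Collection says that the brushing information "will be collected through telephone interviews with parents/caregivers at baseline and at the end of the intervention".
- **Covariates.** Mediators and Confounders lists parent's age, and then "family size, and race/ethnicity will be considered confounders and explored for effect modification". For the youngest group it adds parental education and juice consumption. Child age appears only as a stratifier for the descriptive statistics.
- **Sizing for brushing.** Sample Size: "Assuming a proportion in the passive control group of .6, alpha = .025, beta = .20". This gives 39 and 66 per group for relative effects of 50% and 40%, and 150 per group was chosen.

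**The concern.** Difference-in-differences earns its cost where groups may differ systematically at the start. Randomization already deals with that here. Subtracting the whole baseline value amounts to fixing its regression coefficient at 1. When last year's answer predicts this year's only moderately, that coefficient is too large and the subtraction imports noise. Regression on the baseline estimates the coefficient instead.

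The outcome at stake is parent-reported twice-daily brushing, because it rests on 150 interviews per arm. Its primary contrast is test versus active control, and both of those arms receive the kits. The difference between them could well be smaller than the difference from the passive control for which the sample was sized.

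The plan also treats pre-post change within an arm as an intervention effect and predicts no change in the passive arm. These children are under 36 months at baseline and are seen again 10 months later. Their brushing can change with age without any intervention, so only the contrast between arms isolates the effect.

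**Working it through.** **Step 1. Reproduce the plan's sample sizes.** Inputs from Sample Size: control proportion 0.6, alpha 0.025, power 0.80. Relative effects of 50% and 40% give 0.6 × 1.5 = 0.90 and 0.6 × 1.4 = 0.84, that is, differences of 30 and 24 points. The formula is the follow-up-only comparison of two proportions with pooled variance under the null, two-sided alpha and no continuity correction:

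n = [z(0.9875)·√(2p̄(1−p̄)) + z(0.80)·√(p1(1−p1) + p2(1−p2))]² / (p1−p2)², with z(0.9875) = 2.241 and z(0.80) = 0.842.

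- 0.6 vs 0.90: (2.241 × 0.612 + 0.842 × 0.574)² / 0.09 = 38.3, rounded up to 39.
- 0.6 vs 0.84: (2.241 × 0.635 + 0.842 × 0.612)² / 0.0576 = 65.2, rounded up to 66.

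Both match the plan. No baseline term or correlation is needed to obtain them. The same formula also returns the caries figures of 206 and 113.

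**Step 2. Compare the analyses.** Let rho be the correlation between baseline and follow-up status, with equal variances at both times. Variances relative to follow-up alone:

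- difference-in-differences: 2(1−rho)
- baseline-adjusted: 1−rho²

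The first minus the second is (1−rho)², which is positive for every rho below 1. Their ratio is 2/(1+rho). The first exceeds 1, and so is worse than ignoring the baseline, when rho is below 0.5.

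**Step 3. Put in 150 per arm.** At a proportion of 0.6 the variance is 0.6 × 0.4 = 0.24. The follow-up-only standard error is √(2 × 0.24/150) = 0.0566. The detectable difference is (2.241 + 0.842) × 0.0566 × √f, where f is the relative variance from step 2. For follow-up alone (f = 1) this is 17.4 points, and power for a 15-point difference is 66%. Rho is not in the document, so the values below are assumptions. DiD stands for difference-in-differences.

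| rho (assumed) | f, DiD | f, adjusted | Variance ratio | Detectable difference in points, DiD vs adjusted | Power for 15 points, DiD vs adjusted |
|---|---|---|---|---|---|
| 0.3 | 1.40 | 0.91 | 1.54 | 20.6 vs 16.6 | 50% vs 71% |
| 0.5 | 1.00 | 0.75 | 1.33 | 17.4 vs 15.1 | 66% vs 79% |
| 0.7 | 0.60 | 0.51 | 1.18 | 13.5 vs 12.5 | 88% vs 93% |

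The 15-point difference is illustrative and is not a figure from the plan. At rho = 0.3, 150 interviews are worth 150/1.40 = 107 under DiD and 150/0.91 = 165 under adjustment.

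**Step 4. Check the plan's own effects.** With the same variance of 0.24 and rho = 0.3, the DiD standard error is 0.0566 × √1.4 = 0.0669.

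- 24 points: 0.24/0.0669 − 2.241 = 1.34, power about 91% (about 99% under adjustment).
- 30 points: 0.30/0.0669 − 2.241 = 2.24, power about 99%.

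Even at rho = 0 the effective size is 150/2 = 75 per arm, still above the required 66.

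**The case against.** The strongest reply has four parts.

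1. **The sizing has room to spare.** 150 were chosen where 66 would do, and the plan's own effects remain well powered. This stands, and it limits the point to efficiency.
2. **The brushing hypothesis is itself about change, and DiD is unbiased under randomization.** Both are true. It also removes any ageing trend shared by the arms, so the ageing problem affects only the within-arm reading. But a comparison of follow-up status adjusted for baseline answers the same between-arm question with less variance.
3. **The formulas are for linear change scores, while the plan uses logistic regression for binary outcomes.** This is also fair: the ratios are approximate.
4. **Covariates may be settled in an analysis plan that is not shown.** So the absence of child age from the list is not counted as an error. The choice of DiD, however, is stated in the article.

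Two stronger readings are tempting and are not supported.

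- **Infants' baselines are necessarily zero, and this is why precision is lost.** The document never says so, and for brushing it sits badly with the 0.6 assumed for the passive arm. The mechanism also fails: a constant zero has no variance, so subtracting it costs nothing and adjusting for it gains nothing. In a simulation with every baseline at zero, follow-up-only, DiD and baseline-adjusted analyses all had a standard error of about 0.053.
- **Both primary comparisons lose power.** The restorative hypothesis is worded as a post-start count, test against active control, with about 10,800 families in each of those arms (Trial Status). No loss has been shown there.

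**Conclusion.** The point holds for the toothbrushing primary outcome, as an efficiency weakness. The plan names difference-in-differences for randomized arms, while its sample size reproduces as a plain follow-up comparison. Where baseline brushing varies, a baseline-adjusted comparison is more precise at any correlation below 1. The gain in detectable difference runs from about 4 points at rho = 0.3 (20.6 − 16.6) to about 1 point at rho = 0.7 (13.5 − 12.5).

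These sizes rest on an assumed rho, equal pre and post variances, a proportion near 0.6, 150 analysed per arm and a linear approximation. There is no bias in the between-arm contrast, and no stated figure is wrong. The loss matters chiefly if the difference between test and active control is smaller than the 24 to 30 points used for sizing. Separately, change within one arm should not be read as an effect of the intervention.

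**What to change.** - **Toothbrushing, primary analysis.** Specify a between-arm logistic regression of 10-month twice-daily brushing status on arm, baseline brushing status and child age, with test versus active control as the primary contrast.
- **Within-arm change.** Report pre-post change in each arm, including the passive control, as description only.
- **Restorative care.** Compare the counts over the 18 months after the start between test and active control, as the hypothesis is worded, with child age as a covariate. If a pre-period count is also used, do not code a child who has no pre-period as a true zero.

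The cost is a change of analysis wording. Baseline brushing is already collected in the first interview, and age is needed to establish eligibility. No new data, contacts or participants are required.

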### Study Measures and Data Collection

#### Outcomes

The primary outcome for all children less than 21 years old will be restorative dental care received as a proxy for the presence of dental caries. Additionally, for children less than 36 months old at baseline, the other primary outcome will be parent/caregiver reported frequency of twice daily toothbrushing the child’s teeth. Secondary and tertiary outcomes will be cost of dental care for all participants; and, only for children less than 36 months old at baseline, parent/caregiver-reported oral-health related quality of life of the child, satisfaction with the program, and dental caries (tooth decay).

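### Families are randomized but restorative care is worded per child: the protocol should fix the unit of analysis and, if it is the child, allow for siblings

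*Protocol article*

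**What the plan says.** All references are to the protocol article.

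- **Unit of allocation.** Randomization and Blinding: "Families will be randomized with equal probability to one of three study conditions using computer-generated random numbers". Trial Status counts the randomized units as 21,743 families, with 10,797 in the test arm and 10,796 in the active control arm.
- **Unit of the outcome.** Outcomes: "The primary outcome for all children less than 21 years old will be restorative dental care received". Eligibility, under Selection of Participants, is also defined child by child.
- **Primary comparison.** Statistical Analysis Plan: the hypothesis is that "the test intervention group will have a lower number of restorative dental care procedures received than the active control group", over 18 months. It is stated for all participants, and that word is not defined as child or family.
- **Models.** Statistical Analysis Plan: difference-in-difference models are named, and then "Linear regression will be used to evaluate continuous outcomes and logistic regression will be used to evaluate binary outcomes". Neither this section nor Sample Size mentions family, intraclass correlation, GEE, random effects or robust variance.
- **Family size.** The Toothbrushing Kit: "the average family served by Advantage Dental Services has 3 or 4 children".
- **Count of units.** Selection of Participants gives the study population as roughly 20,000 families. Sample Size makes no calculation for dental care outcomes and says that "the sample size of 20,000 participants was deemed sufficient to observe an effect of the intervention".

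**The concern.** Siblings share an allocation, a mailed kit, the parents who receive the messages and, very plausibly, diet, brushing habits and access to a dentist. Their restorative-care counts and costs are therefore likely to be positively correlated. If each child is one record and the model assumes independence, the variance of the difference between arms is understated and false positives become more frequent.

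Test versus active control is the comparison that isolates the messages and telephone support. The Discussion says the results will be used to decide whether that component is needed or can be dropped, so a false positive here has a direct practical consequence.

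The wording adds a second difficulty. The same figure of about 20,000 is called families in one section and participants in another, and it is the only support offered for the adequacy of the sample on this outcome. A reader cannot tell whether the analysis set is some 20,000 families or a possibly much larger number of children.

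**Working it through.** **1. The plan's own sample sizes.** Two-proportion formula, pooled variance under the null, no continuity correction, two-sided alpha 0.025 (z = 2.2414), power 0.80 (z = 0.8416):

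n = [z(1−α/2)·√(2·p̄·(1−p̄)) + z(1−β)·√(p1(1−p1) + p2(1−p2))]² / (p1 − p2)²

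| Outcome | p1 vs p2 | Computed n per group | Stated |
|---|---|---|---|
| Toothbrushing, 50% effect | 0.60 vs 0.90 | 39 | 39 |
| Toothbrushing, 40% effect | 0.60 vs 0.84 | 66 | 66 |
| Caries, 30% effect | 0.50 vs 0.35 | 206 | 206 |
| Caries, 40% effect | 0.50 vs 0.30 | 113 | 113 |

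All four reproduce with independent observations and a design effect of 1. They concern toothbrushing and caries, so they neither prove nor refute anything about restorative care, for which no figure is given.

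**2. Effect of treating siblings as independent.** Inputs: children per family m = 3 to 4 (from The Toothbrushing Kit, used here as an assumption about the analysed children) and intra-family correlation ICC = 0.05 to 0.30 (assumption; the article gives none). The formulas take families of equal size:

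- design effect DE = 1 + (m − 1)·ICC
- naive SE / true SE = 1/√DE
- true type I error of a nominal two-sided 5% test = 2·[1 − Φ(1.96/√DE)]

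| m | ICC | DE | Naive SE / true SE | Type I error |
|---|---|---|---|---|
| 3 | 0.05 | 1 + 2×0.05 = 1.10 | 0.953 | 6.2% |
| 3 | 0.30 | 1 + 2×0.30 = 1.60 | 0.791 | 12.1% |
| 3.5 | 0.10 | 1 + 2.5×0.10 = 1.25 | 0.894 | 8.0% |
| 3.5 | 0.20 | 1 + 2.5×0.20 = 1.50 | 0.816 | 11.0% |
| 4 | 0.05 | 1 + 3×0.05 = 1.15 | 0.933 | 6.8% |
| 4 | 0.30 | 1 + 3×0.30 = 1.90 | 0.725 | 15.5% |
| 1 (one child or one total per family) | any | 1.00 | 1.000 | 5.0% |

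Over this range, the coverage of a nominal 95% interval runs from 93.8% down to 84.5%.

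**3. How firm is m?** Trial Status reports 2857 of 21,743 families with a child under 36 months: 2857/21,743 = 13.1%. As a rough check, assume ages spread evenly over 0 to 20 years and independent between siblings. The share of families with at least one such child is then 1 − (18/21)^m:

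- m = 1: 14%
- m = 3: 37%
- m = 4: 46%

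The reported share fits poorly with 3 to 4 eligible children per unit. Either families have fewer eligible children than the kit section suggests, or the units called families are partly children. With m = 2 and ICC 0.05 to 0.30, DE is 1.05 to 1.30 and the type I error is 5.6% to 8.6%. With m = 1.5 it is 5.3% to 6.8%.

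**The case against.** The strongest objection is that the article names types of model and is silent on how their variance is estimated. GEE and family-clustered standard errors are still linear or logistic regression and would fit the quoted sentence. A condensed article may leave such detail to a fuller plan. This stands against the stronger reading that a reader might infer, namely that the trial ignores clustering and that its confidence intervals are too narrow. The article never says that records will be treated as independent.

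Second, the unit may be the family. Trial Status uses participants for families, and the hypothesis is stated for participants. With one total per family, the inflation disappears. This also stands, and it is why the finding is conditional. It does not remove the need for a correction, because the Outcomes section would then have to be reworded.

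Third, the family size describes all families served and was used to decide what goes in the kit; the ICC has no source in the article. Both objections stand, so the size of the effect is a range under assumptions.

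Fourth, the finding should not be stretched to the toothbrushing outcome. That outcome comes from 450 interviewed parents or caregivers, 150 per arm, apparently one per family although the article does not say so. It is probably little affected.

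Two further inferences are not supported. One is that a count model with an enrolled-time offset is required. The plan already speaks of rates, unequal enrolment is not stated, and a linear comparison of mean counts is valid in arms of this size. The other is that clustering would let trivial differences reach significance. That follows from the large sample, not from clustering.

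**Conclusion.** The point holds conditionally. Allocation is by family, the restorative-care outcome is worded per child, multi-child families are described as typical, and the named models carry no stated allowance for family. Applied to child records as they stand, those models would give standard errors that are too small whenever siblings are positively correlated. This affects test versus active control on restorative care, and the cost comparisons.

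Under the assumed 3 to 4 children and ICC of 0.05 to 0.30, the true standard error is 1.05 to 1.38 times the naive one, and a nominal 5% test errs about 6% to 16% of the time. With fewer eligible children per family, as the under-36-month count hints, the inflation is smaller. No single corrected figure can be derived from the article.

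The inconsistency over the unit does not depend on any assumption. About 20,000 units are families in one section and participants in another. This is a contradiction in the text, not a detail left to a later plan.

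**What to change.** - State the unit of analysis for restorative care and for costs.
- If it is the child, specify family-clustered robust variance, GEE with family as the cluster, or a random family effect. Apply it to restorative care, costs and any other child-level outcome where a family can contribute more than one child. Clustering the robust variance on family also covers the pre and post records of one child in the difference-in-difference models, because they nest within the family.
- If it is the family, say so, and reword the outcome as a total or mean per family.
- Reconcile families with participants in Selection of Participants, Sample Size and Trial Status, and report the number of families and of children in each arm.

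The cost is a few sentences and one option in the software, with no new data. With a child-level analysis, confidence intervals become somewhat wider. A Poisson or negative binomial model with an enrolled-time offset may be chosen, but it is optional and does not form part of this correction.
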